# Effects of two neuromuscular training programs on running biomechanics with load carriage: a study protocol for a randomised controlled trial

**DOI:** 10.1186/s12891-016-1271-9

**Published:** 2016-10-22

**Keywords:** Running biomechanics, Load carriage, Randomized clinical trial, Neuromuscular training, Resistance training

## Abstract

**Background:**

In recent years, athletes have ventured into ultra-endurance and adventure racing events, which tests their ability to race, navigate, and survive. These events often require race participants to carry some form of load, to bear equipment for navigation and survival purposes. Previous studies have reported specific alterations in biomechanics when running with load which potentially influence running performance and injury risk. We hypothesize that a biomechanically informed neuromuscular training program would optimize running mechanics during load carriage to a greater extent than a generic strength training program.

**Methods:**

This will be a two group, parallel randomized controlled trial design, with single assessor blinding. Thirty healthy runners will be recruited to participate in a six weeks neuromuscular training program. Participants will be randomized into either a generic training group, or a biomechanically informed training group. Primary outcomes include self-determined running velocity with a 20 % body weight load, jump power, hopping leg stiffness, knee extensor and triceps-surae strength. Secondary outcomes include running kinetics and kinematics. Assessments will occur at baseline and post-training.

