### Sample size calculation

This study was powered on the effects of a core stability program on changes to hopping leg stiffness [26]. Sample size was planned based on a two way, repeated measures ANOVA, using the Hotelling-Lawley Trace to test for an intervention by time interaction [27]. Previous studies on leg stiffness reported a standard deviation of 3600 N/m [26], and a correlation between repeated measures of 0.80 [28]. For a desired power of 0.80, and a Type 1 error rate of 0.05, 24 participants are needed to detect a between group mean difference of 3000 N/m. In order to account for a 20 % dropout over the six week intervention period, 30 participants will be tested.

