### Three dimensional motion capture – jumping and hopping protocol

Squat jumps (SJ), countermovement jumps (CMJ), and single leg vertical hoping (SL hop) will be performed on the force plates. For both the SJ and CMJ, the assessor will demonstrate and instruct technique, and participants will have to practise these jump techniques until performance is stable. For all tests, participants will be required to fix their arms at 90° abduction (“T” pose), to limit the influence of upper body on jump performance [34]. For the SJ, participants will perform a maximal concentric vertical jump from an initial squat depth of approximately 90° knee angle (visual estimation). For the CMJ, participants will descend into a squat depth of approximately 90° knee angle (visual estimation), followed without pause by a rapid maximal vertical jump and landing in a comfortable squat position [35]. When the assessor is satisfied with the practice performances, three maximal SJ trials and three maximal CMJ trials will be performed and recorded. Both SJ and CMJ will be performed with and without an external 20 % BW load. Each trial will be interspersed with a 30s rest and each test interspersed with a one minute rest to avoid fatigue. SL hopping will be performed for both legs separately over four conditions: 1) self-paced hopping frequency (BW), 2) self-paced hopping frequency with 20 % BW carriage, 3) hopping at a frequency of 3.0 Hz (BW), and 4) hopping at a frequency of 3.0 Hz with 20 % BW. Hopping frequency will be set using a handheld digital metronome. Each hop condition will last 10 s, with a one minute break interspersed [36]. Trials will be repeated if hopping frequency is not maintained. The order of testing will be randomized using an online random sequence generator (https://www.randomizer.org/).

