### Dependent variables and statistics

For the SJ and CMJ, peak power using inverse dynamics and the force plate approach will be derived [60]. For SL hopping, leg stiffness at each condition will be derived. For the self-paced running tasks with and without load carriage, average self-paced running velocity will be derived over a complete stride. Discrete variables of individual joint positive and negative work, total and net joint work for stance and swing phase of all running trials will be derived. Spatio-temporal variables of stance and swing duration, stride length, and cadence will be derived for all running trials. Time series of the three dimensional joint angles, moments, and powers of all three joints will be extracted for all running trials. Three-dimensional leg stiffness in running will be calculated in a three-step process from an adapted method in a previous study [61]. First, a three dimensional leg length will be defined as the vector from the hip joint centre to the centre of pressure. Second, the component of the resultant three dimensional ground reaction force (GRF) projected onto the leg vector will be calculated (taking the dot product of the GRF vector with the unit vector of the leg). Lastly, leg stiffness will be derived using the ratio of projected GRF (at the time of peak resultant GRF) to the change in leg length (between initial contact to peak GRF). For strength analysis, average peak concentric torque and power, and absolute peak concentric torque and power, of the knee extensors and ankle plantar flexors will be extracted.

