Descriptive statistics (mean and standard deviation) will be calculated for baseline demographics of participants. Between groups difference in baseline demographics will be calculated using *t*-test or non-parametric test where appropriate. Analysis will be based on an intention-to-treat (ITT) using the multiple imputation method [62]. A repeated measures linear mixed model with time, group, and their interaction as fixed effects, and participants clustered within groups as random effects will be used to analyse our discrete dependent variables [63]. For the linear mixed model, significance will be set at α = 0.05. Descriptive statistics and linear mixed modelling will be performed in R software within RStudio (Version 0.98.1062, RStudio, Inc.). Statistical testing between group and within group mechanical wave form data (kinematics, kinetics) will be analysed using Statistical Parametric Mapping (SPM). Statistical significance will be inferred using Random Field Theory (RFT), with appropriate Bonferroni correction applied to retain a family-wise error rate of α = 0.05. SPM will be performed using the latest version of spm1d package (www.spm1d.org), installed in Python 2.7, and implemented in Enthought Canopy 1.5.4 (Enthought Inc., Austin, USA).

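### Five unranked primary outcomes are tested at an unadjusted 0.05, while the plan's only family-wise correction is reserved for secondary waveforms

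*Protocol article*

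**What the plan says.** The abstract (Methods) gives the list: "Primary outcomes include self-determined running velocity with a 20 % body weight load, jump power, hopping leg stiffness, knee extensor and triceps-surae strength". That is five constructs. Running kinetics and kinematics are named as secondary. The Objectives section does not rank the outcomes either.

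Dependent variables and statistics describes a mixed model with time, group and their interaction, which "will be used to analyse our discrete dependent variables". Its error rate is fixed in one sentence: "For the linear mixed model, significance will be set at α = 0.05". The waveform data go to statistical parametric mapping, "with appropriate Bonferroni correction applied to retain a family-wise error rate of α = 0.05". No other multiplicity rule appears.

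Four of the five constructs are measured in several versions. For hopping, "SL hopping will be performed for both legs separately over four conditions". Jump power comes from two jumps, each with and without load, and the statistics section names two ways of deriving it. Strength yields "average peak concentric torque and power, and absolute peak concentric torque and power" for two muscle groups, and the dynamometry section provides rest between sides.

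Sample size calculation rests on hopping leg stiffness alone, at a Type 1 error rate of 0.05: "24 participants are needed to detect a between group mean difference of 3000 N/m". It does not call stiffness the single primary outcome, and does not say which leg or hopping condition is meant.

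**The concern.** With five primary outcomes of equal standing, each at 0.05, the 5% error rate belongs to a single test and not to the set of primary results. The only family-wise protection covers secondary waveforms, so the primary outcomes are held to a looser standard than part of the secondary ones.

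This matters more than usual here because the outcomes could favour different arms. The biomechanically informed group trains single-leg hopping and countermovement jumps, which are also test tasks. The generic group trains heavy leg press, calf raises and lunges, which lie closer to the strength tests. Split results are plausible, and the article does not say which outcome would settle the hypothesis that the informed programme is better. The planned 80% power also applies to one construct only, in a version not identified.

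**Working it through.** **1. Reproducing the sample size.** Inputs from Sample size calculation: SD 3600 N/m, correlation 0.80, difference 3000 N/m, power 0.80, alpha 0.05 (taken as two-sided; the article does not say). With two time points and two groups, the group-by-time interaction is a two-sample t-test on change scores.

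- SD of change = 3600 × √(2 × (1 − 0.80)) = 2276.8 N/m.
- The noncentral t distribution gives 11 per arm, 22 in all, close to the stated 24.
- At 12 per arm the noncentrality is 3000 / (2276.8 × √(2/12)) = 3.23, and power is 0.87.
- Dropout: 24 / (1 − 0.20) = 30, as stated.

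The sample size is therefore sound for the one test it covers.

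**2. Family-wise error over five outcomes, one variable each.** For independent tests the rate is 1 − (1 − 0.05)^5 = 1 − 0.774 = 22.6%. The article gives no correlations between outcomes, so a range was assumed and equicorrelated normal test statistics were simulated, rejecting when |Z| > 1.96:

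| Assumed pairwise correlation | Chance of at least one false positive |
|---|---|
| 0 | 22.6% |
| 0.3 | 21% |
| 0.5 | 18% |
| 0.7 | 15% |
| 0.8 | 13% |

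**3. How many versions could be tested.**

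- Widest reading: 1 velocity + 8 jump power (2 jumps × 2 loads × 2 methods) + 8 hopping stiffness (4 conditions × 2 legs) + 16 strength (2 muscles × 2 sides × 4 measures) = 33.
- One jump-power method and one side for strength: 1 + 4 + 8 + 8 = 21.

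For 33 tests the rate is 1 − 0.95^33 = 81.6% under independence. It is about 67%, 54%, 48% and 34% for within-construct/between-construct correlations of 0.5/0.2, 0.7/0.3, 0.8/0.3 and 0.9/0.5. For 21 independent tests it is 65.9%. These figures apply only if every version is tested as a primary outcome.

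**4. What adjustment costs.** The first Holm step over five outcomes is 0.05 / 5 = 0.01. On the inputs of step 1:

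| Evaluable | Power at 0.05 | Power at 0.01 |
|---|---|---|
| 24 | 87% | 66% |
| 30 (no dropout) | 94% | 79% |

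To reach 80% power at 0.01 takes 16 per arm, so 32 evaluable and 32 / 0.8 = 40 recruited.

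**The case against.** **A condensed article may leave multiplicity to an analysis plan.** That would answer silence, but the article is not silent. It fixes 0.05 for the discrete variables and places family-wise control elsewhere. Which version represents each construct is more fairly a detail for the fuller document, so the finding does not rest on it.

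**Hopping stiffness may be the implicit primary outcome,** since the trial is powered on it. The article never says so, and stiffness has eight leg-by-condition versions.

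**The Discussion promises only preliminary evidence.** This softens the conclusions to be drawn, but neither changes the error rate nor ranks the outcomes.

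A reader might infer more than the text supports, in three ways.

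- *That 33 primary tests are planned and a false positive is therefore likely, at 82%.* The article lists what will be derived or extracted; it does not call each item a separate primary test. The two sides for strength are inferred from a rest period, the two jump-power methods might be one procedure, and legs or conditions could be averaged. The 82% also assumes independence between closely related measures on the same person.
- *That one significant result would become a claim that one programme is better.* The article states no decision rule, so this cannot be read from it.
- *That adjustment takes power from 80% to 66%.* This sets a planning target against a recomputed value. The like-for-like change with 24 evaluable is 87% to 66%.

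**Conclusion.** The point holds for the five named outcomes. As written, the plan gives about a 13% to 23% chance of at least one false-positive primary result when the programmes do not differ, against a nominal 5%. This assumes one variable per construct, two-sided tests and pairwise correlations between 0 and 0.8; the correlations are assumptions. Testing several versions of a construct would raise the figure, but the article does not establish how many would be tested. The sample size calculation reproduces closely and is not at fault; it simply covers one of the five outcomes, in an unspecified version.

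**What to change.** Before unblinding, adopt one of two rules and update the registry entry to match.

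(a) Name one primary variable at 0.05 and make the other four constructs secondary. One fixed version of hopping leg stiffness is the natural choice, because 24 evaluable and 30 recruited were calculated for it. If the investigators prefer loaded running velocity, they need to give its own power basis: the article states no SD, correlation or target difference for it.

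(b) Keep all five as primary, fix one participant-level variable for each in advance (load, leg or side, condition, measure and method of derivation), and test the five with Holm.

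Under either rule, label the remaining versions exploratory and state that the 80% power refers to hopping stiffness only.

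The change is one of wording. The price is that fewer outcomes can carry a confirmatory claim. Rule (a) leaves the sample size as it is if stiffness is chosen. Rule (b) accepts the lower power at the strictest Holm step shown in the working, or requires more participants.

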**Discussion:**

To our knowledge, no training programs are available that specifically targets a runner’s ability to carry load while running. This will provide sport scientists and coaches with a foundation to base their exercise prescription on.

**Trial registration:**

ANZCTR (ACTRN12616000023459) (14 Jan 2016)

**Electronic supplementary material:**

The online version of this article (doi:10.1186/s12891-016-1271-9) contains supplementary material, which is available to authorized users.

## Background

Ever since the “Battle of Marathon” between Greece and Persia was recorded [1], the accomplishment of running a 42 km marathon is seen as the ultimate achievement for a distance runner. However, the last two decades has seen both recreational and elite level runners striving for distances well beyond a standard marathon. Interest and participation in ultra-endurance races [2], multi-stage racing events [3], and off-terrain trail and adventure races have risen [4] as individuals seek new ways to challenge human limits. These races not only test a runner’s speed and endurance, but also their ability to navigate and survive over undulating terrains and harsh environments [3]. Navigation and survival requires routine access to specialized equipment and sustenance. This requirement necessitates athletes to compete with externally carried loads [5]. Few studies have considered the role of load carriage on the potential impact on a runner’s health and performance [6]. In addition, no studies have considered if runners can be trained to adapt to external loads in running.

Load carriage in running poses two fundamental problems to athletes and occupational personnel: 1) an increased injury rate, 2) and increased metabolic energy expenditure that may reduce performance [7]. In the adult population, the increased overuse injury rate associated with load carriage has largely been investigated in the military setting, where load carriage biomechanics have been predominantly investigated while walking [7]. A previous study reported that 8 % of the 5000 injuries reported in the Australian Defence Force from January 2009 to December 2010, were related to heavy load carriage [8]. Of these injuries, 56 % affected the lower limb and were classified as muscular stress related [8]. Although no causative studies have been performed, it is likely that load carriage while running may exacerbate the already high incidence of running related injuries [9]. In addition, when an individual runs with load, the energy demand involved in maintaining constant running speed is increased [10]. Minimising the reduction in running speed associated with load carriage is important for the survivability of military personnel, the performance of athletes, and the overall efficiency of movement in recreational runners [11, 12].

The risk of injury and reduced performance associated with load carriage in running, points to the need for a preconditioning program for these athletes. There is convincing evidence that resistance based neuromuscular training programs are effective at reducing running related injuries (RRI) during body weight (BW) running (i.e. running with no external load) [13], and improving BW running performance [14]. However, current training programs have been developed using BW running research [15, 16], rather than loaded running research. The only studies that have attempted to define best training practices for load carriage gait has been performed in the military setting [17]. A limitation in existing training studies has been that exercise prescription has not been explicitly informed from biomechanical studies of load carriage gait. Rather, training was of a generalised nature, targeting the large muscle groups of the lower limb [17]. The type of exercises and mode of contractions used for preconditioning programs should be specific to the gait pattern required for athletes, and be based on prior knowledge of biomechanical adaptations during load carriage.

### Potential adaptive and mal-adaptive biomechanics

Studies using computed muscle control and induced acceleration analysis have identified the integrated roles of lower limb muscles in BW running. Collectively, the functions of these muscles are to provide a vertical force to accelerate/decelerate body weight, and horizontal forces to accelerate/decelerate inertial mass [18, 19]. When additional load is imposed on a runner, greater vertical and horizontal forces are needed to accelerate and decelerate an increased total weight and total inertial mass, respectively. Biomechanical changes to running with load are classified as adaptive if they enable an increase in baseline motor function (Table 1). For example, an increase in ankle power absorption in mid stance with load may be adaptive as it transfers power away from proximal segments to the foot [6]. This may aid in increased elastic-energy recovery at the ankle plantar flexor muscle-tendon unit, which may be essential to sustain faster running velocities during load carriage.

**Table 1 Tab1:** Biomechanical adaptations of load carriage to potentially optimize metabolic cost and minimise injury risk

Potential positive adaptation	Biomechanical changes with load	Potential negative adaptation
• Transfer energy from proximal to foot segment [64] • ↑ Energy stored as elastic energy [65]	↑ Ankle negative power mid-stance [6]	
• Accelerates leg into extension to ↑ energy transferred to proximal segments [64]	↑ Knee positive power late stance [6]	
• ↑ Hip extension deceleration of trailing thigh segment for preparation into hip flexion swing [66] • Transfers energy from trunk to trailing stance limb to prepare into swing [64]	↑ Hip negative power late stance [6]	
• ↑ Elastic energy recovery [67] • Avoid excessive vertical COM excursion and maintain ground reaction force alignment to stance limb [68, 69]	↑ Leg stiffness [70]	
• Architecture of triceps-surae muscle tendon unit makes it an efficient force generator [65]	Small role for inter-joint work redistribution [71]	
	↑ Hip adduction late stance [6]	• Asymmetrical loading on knee soft tissues [72]
	↑ Knee and ankle flexion mid-stance [6]	• ↑ COM vertical excursion [70] • ↑ Patellofemoral joint compression pressure and ↑ Achilles tendon compression [73, 74]

↑ = Increase; ↓ = Decrease

On the contrary not all biomechanical changes with load may be adaptive. Some mechanical changes are likely to be mal-adaptive as they may contribute to a greater risk of incurring RRI or represent an inefficient running style. Poor hip control of non-sagittal plane rotations has been documented to increase the risk of developing RRIs [20]. At the kinematic level, load carriage has been associated with increased hip adduction at terminal stance [6] (Table 1). This increase in non-sagittal plane movements may represent suboptimal muscle capacity and motor control [21]. In addition, poor proximal trunk-pelvis control in running may result in energy being wasted in maintaining postural balance and inter-segmental alignment. Remediating mal-adaptive mechanical changes whilst enhancing adaptive changes could improve biomechanical indices of running performance and injury risk during load carriage.

### Rationale

Load carriage in running is increasingly common in running related sports. The ability to positively and predictably adapt to the imposed load when running necessitates an evidence-based training program. Existing training studies for load carriage performance in the military setting cannot be immediately applied to load carriage running, as most studies investigated performance in walking. This is because running and walking involve different movement dynamics, making the extrapolation of results from walking studies problematic when applied to running. For example, the hip contributes approximately 20 % of total positive power in the stance phase of BW walking, but less than 10 % of total positive power in the same phase of BW running [22]. Second, studies that have investigated ways to improve load carriage performance have adopted a non-randomized design [17]. Reported effect sizes of benefit in intervention studies were larger in trials without a randomized design compared to one with a randomized design [23]. Lastly, studies on load carriage do not appear to specifically target the known neuromuscular demands of load carriage gait patterns [17]. Therefore, the purpose of this investigation is to compare the effects of a biomechanically informed neuromuscular training program to a generic standard best-practice resistance training program on changes in the biomechanics of running with load.

### Objectives

To compare changes in (1) self-determined running velocity with and without load carriage, (2) lower limb running kinematics and kinetics, (3) jumping power and hopping stiffness, (4) and isokinetic knee and ankle extensor strength in healthy adult runners participating in a biomechanically informed training program compared to a generic resistance training program. This generic resistance training program may be seen as the current “gold-standard” program based on current best evidence [17].

